###### Dentist study

Dental practices are assigned to a control and intervention group in a 1:1 ratio using a central, web-based tool (randomizer.at) to avoid any manipulation and ensure concealed allocation. Randomization will be stratified by state and use a block-wise randomization process with a varying length of blocks to arrive at groups of equal size and avoid selection bias. Randomization will take place on the practice (cluster) level, so all participants within a given practice will either be part of the intervention or the control group. The randomizing tool will be administered by the evaluating Institute of Medical Biometry at the Heidelberg University Hospital.

##### Sample size calculation

###### General practitioner study

Sample size calculation refers to the primary endpoint and is based on a t-test (α = 0.05; power = 0.8). We assume that HbA1c in the intervention group will decrease on average by 0.2%-points (standard deviation (sd) of 2.3) compared to the control group. The estimator results from the assumption that at least 50% of T2DM-patients have a need for periodontitis therapy [15, 20] and that they’re able to lower their HbA1c by 0.6%-points through therapy [8]. Out of these patients, an assumed 66% will use the referral to a dentist [21]. To account for cluster effects (patients clustered in practices), an intra-class-correlation of 0.03 and a cluster size of 10 patients per practice is assumed. For the control group calculated from claims data, we assume that it contains at least double the number of patients than the intervention group (allocation in a 2:1 ratio for control vs. intervention group). This results in a sample size of 1980 intervention patients (198 practices, 10 patients each) and 3960 control patients. With an assumed drop-out rate of 20%, there will be 2480 intervention patients (248 practices, 10 patients each) and 4950 control patients. Sample size calculation was performed using PASS v16.0.3.

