## Background

The 2021 WHO Resolution on Oral Health resolution emphasizes the need for better integration of oral health and primary health care [1].

Previous evidence suggests that oral diseases and other noncommunicable diseases occur in parallel [2, 3]. Periodontitis is 2–3 times more prevalent in patients suffering from type-2 diabetes mellitus (T2DM) [4]. T2DM-patients have a higher periodontitis risk [5–7]. Among T2DM patients, periodontitis therapy was shown to reduce HbA1c by 0.6%-points up to 12 months [8] as well as healthcare costs [9, 10]. On the other hand, glycemic control in periodontitis patients may be improved by periodontitis therapy [7, 11, 12].

This shows that better integration of T2DM and periodontitis care offers potential to reduce disease burden and costs - yet, the diagnosis and treatment of T2DM and periodontitis are still disintegrated in Germany, which is the context for this study [13]. The number of undiagnosed T2DM-cases amounts to around 2 million and it takes an average 8 years until T2DM is diagnosed [14]. There is also a discrepancy between need and utilization of periodontitis care: While 10 million people suffer from severe periodontitis, there are 1 million reimbursed treatment cases per year [15]. These gaps between need and utilization give raise to avoidable disease burden and costs. To this end, the present paper describes the protocol for practice-based studies on integrated T2DM and periodontitis care in Germany.

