### Statistical hypotheses and analyses

#### General practitioner study

For the primary outcome, we will test the null hypothesis H_0_^HA^: µ_IG_^T1−T0^ = µ_KG_^T1−T0^ against the alternative hypothesis H_1_^HA^: µ_IG_^T1−T0^ ≠ µ_KG_^T1−T0^ on a two-sided significance-level of 5%. µ_IG_^T1−T0^ and µ_KG_^T1−T0^ represent the reduction of the HbA1c-parameter between baseline (T0) and after 4 quarters (T1) in both groups.

Evaluation of the intervention contains descriptive and explorative statistical analyses of gathered study data as well as available claims data. The goal is an independent, scientifically valid and differentiated statement on effectiveness of the intervention regarding a reduction of the HbA1c parameter using an intervention study with parallel control group. The control group will be calculated from insurer claims data as well as DMP-documentation data across insurers. Using their registration number, intervention practices will be removed from the control group data. Study data will be described using descriptive methods.

Primary analysis will be a hierarchical, linear mixed model representing the multi-level structure of the data (level 1: practice, level 2: patient). For the test of H_0_^HA^, the dependent variable will be “reduction of HbA1c between T0 and T1”. The model contains the practice as a random effect and HbA1c at baseline (T0), age, sex, insurance status, state and residential area as fixed effects on the patient level. Here, only variables that are also included in claims data can be used.

It can be assumed that claims data will be complete and missing values will only occur in the additional study data and the questionnaires. Missing values of the primary outcome will be imputed using multiple imputation [27] while accounting for the baseline-variables age, sex, insurance status and residential area. Assumptions on missing values will be analyzed and an alternative procedure to handle missing data, such as an analysis of the full dataset, will be looked into.

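### The GP study's planning difference of 0.2 subtracts nothing for periodontitis therapy among usual-care controls, so the stated 80% power does not follow from the plan's own chain

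*Protocol article*

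**What the plan says.** The sample size section for the GP study in the protocol article is "based on a t-test (α = 0.05; power = 0.8"). The hypothesis section tests "on a two-sided significance-level of 5"%. The planning assumption is that HbA1c in the intervention group "will decrease on average by 0.2%-points (standard deviation (sd) of 2.3) compared to the control group".

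The same section says where the 0.2 comes from:

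- Need: "at least 50% of T2DM-patients have a need for periodontitis therapy".
- Effect: therapy lowers HbA1c by 0.6 percentage points.
- Uptake: "Out of these patients, an assumed 66% will use the referral to a dentist".

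Of the control group, "we assume that it contains at least double the number of patients than the intervention group". The result is 1980 intervention and 3960 control patients, raised to 2480 and 4950 for 20% drop-out.

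Four other places bear on the control group:

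- The Background reports: "While 10 million people suffer from severe periodontitis, there are 1 million reimbursed treatment cases per year".
- Table 1 excludes patients with periodontitis therapy in the 12 months before entry. It places no bar on therapy afterwards.
- The secondary endpoints for GP practices include use of periodontitis therapy, taken from primary and claims data.
- The dentist study's sample size section sets a control diagnosis rate of 0.05 from an internal insurer-data analysis and plans on the difference from 0.10.

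**The concern.** All three factors behind the 0.2 describe the intervention group. No term represents what happens to controls, so the control therapy rate is implicitly zero. Nothing in the article supports zero. The controls are concurrent usual-care patients, the exclusion looks only backwards, and therapy use is a planned outcome measurable in claims data. Any therapy that controls in need receive during follow-up lowers their HbA1c by the same assumed mechanism and narrows the difference.

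This concerns the primary endpoint of a non-randomized comparison. If the planning difference is too large, a null result will be read against 80% power that the stated assumptions do not deliver.

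**Working it through.** **Inputs.** From the GP sample size section: difference 0.2, SD 2.3, alpha 0.05 (two-sided, from the hypothesis section), power 0.80, ICC 0.03, 10 patients per practice, control to intervention 2:1, drop-out 20%; need 0.50, uptake 0.66, effect 0.6.

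**1. The plan's own figures reproduce.**

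- Design effect = 1 + (10 − 1) × 0.03 = 1.27.
- Intervention n before clustering = 1.5 × (1.960 + 0.842)² × 2.3² / 0.2² = 1557.
- With clustering, 1557 × 1.27 = 1977, rounded to 198 practices = 1980, with 3960 controls.
- Drop-out: 1980 / 0.8 = 2475, rounded to 248 practices = 2480; 3960 / 0.8 = 4950.

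The computation from 0.2 onwards is correct. The question is the 0.2 itself.

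**2. The planning difference.** 0.50 × 0.66 × 0.6 = 0.198, rounded to 0.2. No control term enters.

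**3. Net of usual-care therapy.** Let r be the 12-month therapy rate among patients in need under usual care. There are two readings of the 66%:

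- (a) It is total uptake in the intervention group: difference = 0.50 × 0.6 × (0.66 − r).
- (b) It is use of the referral only, and those who do not use it are also treated at rate r: difference = 0.50 × 0.6 × [0.66 + 0.34r − r] = 0.50 × 0.6 × 0.66 × (1 − r).

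**4. A value for r.** The article gives none for this population. The only related figure is in the Background: 1 million / 10 million = about 10% a year. Using it is an assumption; 5% is shown beside it.

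**5. Power** = Φ(difference / SE − 1.960).

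- 1980 vs 3960: SE = 2.3 × √[1.27 × (1/1980 + 1/3960)] = 0.0713.
- 1980 vs 4950 (no control drop-out): SE = 2.3 × √[1.27 × (1/1980 + 1/4950)] = 0.0689.

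| r | Reading | Difference | Power, 3960 controls | Power, 4950 controls |
|---|---|---|---|---|
| plan as stated | – | 0.200 | 80% | 83% |
| 5% | (a) | 0.183 | 73% | 76% |
| 5% | (b) | 0.188 | 75% | 78% |
| 10% | (a) | 0.168 | 65% | 68% |
| 10% | (b) | 0.178 | 70% | 73% |

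With 3960 controls, rates of 15% and 20% give 57% and 49% under reading (a), and 66% and 60% under (b).

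**6. More controls.** At a difference of 0.168, with 10 controls per practice, 5:1 (9900 controls) gives 75% and 10:1 (19800) gives about 79%. If taking more controls means 50 per practice, their design effect is 1 + 49 × 0.03 = 2.47, and these fall to 69% and 75%. The size of the claims pool is not stated, so the ratios are illustrative.

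**The case against.** Several points on the other side are sound.

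- **The 10% is not a rate for this population.** It sets national reimbursed treatment cases against people with severe periodontitis, while the sample size section speaks of need for therapy among T2DM patients. Excluding recently treated patients may also select people who use such care less. This stands, and it is why the result is a range tied to an assumed rate.
- **Both arms receive usual care.** After T0 all patients do, so intervention patients who do not use the referral may be treated too. This is reading (b), and it raises power at 10% from 65% to 70%.
- **Claims controls need not drop out.** The analysis section expects claims data to be complete. Keeping 4950 controls adds about 3 percentage points.
- **Need is given as a floor.** At r = 10%, a need of 0.2 / (0.6 × 0.56) = 59.5% under (a), or 0.2 / (0.6 × 0.594) = 56% under (b), restores 0.2. But the plan computes with 50%. In the other direction, its chain counts every used referral as completed therapy with the full effect.
- **The primary model adjusts for baseline HbA1c and other covariates.** If they explained 20% of the outcome variance (an assumption; the article gives no figure), power at 10% would be 75% under (a) and 80% under (b). The plan does not claim this gain; its calculation is an unadjusted t-test.

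A reader might infer that the article's own usual-care figures put power at 65%. They do not. It contains no such rate for the trial population, and 65% is the low end at an assumed 10%. A reader might also infer that the sample size arithmetic is wrong, or that a larger control pool would restore 80% at no cost. The arithmetic reproduces, and step 6 does not support the second inference.

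**Conclusion.** The point holds as a defect in the effect input. The 0.2 is an intervention-group quantity used as a between-group difference, with an unstated control therapy rate of zero that the article's own description of the controls does not support. At the plan's stated inputs the direction is clear: any usual-care therapy rate above zero reduces the difference.

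The size is uncertain because the rate is not given. Across assumed rates of 5% to 10%, both readings of the 66% and either control count, power runs from about 65% to 78%, against the stated 80%. This rests on 50% need, the full 0.6 effect in everyone treated, SD 2.3, the design effect of 1.27 in both groups, and no gain from covariate adjustment.

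**What to change.** In the GP sample size section, state the control-group therapy rate that is assumed. Take it from the claims data as the 12-month periodontitis-therapy rate among patients who would be eligible as controls, just as the dentist study took its control rate from insurer data. Say whether the 66% is total uptake or referral use only. Then restate the planning difference and power as net of that rate, with a range.

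Optionally, use more than two eligible controls per intervention patient where the data allow; the present wording already permits it. Compute that power with the actual control cluster sizes, keep the controls comparable to the intervention group as the plan intends, and do not claim that this step alone brings power back to 80%.

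The cost is one claims query, a revised paragraph and probably a less favourable stated power. The restatement itself requires no additional recruitment.

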###### Dentist study

Sample size calculation refers to the primary endpoint and is therefore based on a Z-Test with non-pooled variance. We assume that, compared to the control group, the rate of new diabetes diagnoses will be 0.1 in the intervention group during the next 4 quarters [22]. For the control group we assume a rate of 0.05 (calculated from an internal analysis of insurer-data for the areas the study will be performed in). It is therefore assumed that the intervention allows for an additional 5% of diabetes diagnoses. Sample size is calculated with α = 5% and power = 80%. Patients are clustered in practices, so an intra-class-correlation of 0.03 and a cluster size of 8 patients per practice is assumed. Assuming an allocation ratio of 1:1 for control vs. intervention group, this results in a sample size of 528 patients (66 practices, 8 patients each) per group. With an assumed drop-out rate of 20%, sample size in each group will be 664 patients (83 practices, 8 patients each), adding up to a total of 1328 patients in 166 practices. Sample size calculation was performed using PASS v16.0.3.

##### Recruitment

Recruitment in the GP study will be actively supported by the Association of Statutory Health Insurance Physicians in the state of Baden-Württemberg (KVBW), the research network of general practitioners in the state of North Rhine-Westphalia (HAFO.NRW), the network of research practices at the Heidelberg University Hospital (FoPra.HD) and the Association of General Practitioners in Baden-Württemberg. Recruitment in the dentist study will be supported by the Association of Statutory Health Insurance Dentists in the state of Baden-Württemberg (KZVBW) and North Rhine-Westphalia (KZVNR).

We will distribute a short invitation letter or fax containing an overview of the study (contents, duration, conditions, compensation for expenses). Practice owners will be asked to indicate whether they’re interested in participating and return the letter via fax or e-mail. Phone calls will be arranged to provide further information to practices that are interested in participation. Information material will be provided to the practice beforehand. The practice receives:

Detailed study information.Informed consent forms for the practice owner, the assistant who will take care of the project and for possible further physicians in the practice.The required authorization form to include the practice in the care contract with the insurer (intervention groups only).

As soon as the authorization form and each form of consent is returned dated and signed by the respective person, the practice is included in the study. They then receive:

Their unique alphanumeric practice ID.A study folder containing countersigned copies of the practice documents as well as guidance and other legally required documents.A patient folder containing the documents to perform the study in the practice (background information for patients, informed consent forms, questionnaires).Log-in data for the research database where practice and questionnaire data will be documented.

When first using the research database, practices need to enter basic data on the practice (size, type, population density, year of establishment, patients per quarter). Afterwards, they may start recruiting patients.

Recruitment and data collection/transfer will be performed by the medical/dental assistant named as the responsible person for the study within the practice. They receive an online video tutorial on how to implement the components of the study.

Medical/dental assistants identify eligible patients according to the inclusion criteria (Table 1) when they visit the practice. They verbally inform these patients about the study, hand out the documents necessary for participation and respond to potential questions. Patients partake in the study by signing the informed consent form. The form will be countersigned by the assistant and the patient receives a copy. Directly afterwards, the baseline survey (T0) takes place.

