##### Baseline survey (T0)

Patients in both studies receive a written questionnaire on sociodemographic data and a self-disclosure of medical conditions. The questionnaire further contains a question on current, subjective health, translated from the publicly available, validated Short Form 36 (SF-36)-questionnaire by RAND Corporation [23]. Additionally, the questionnaire contains the respective questions for periodontitis/T2DM risk assessment (in the dentist study, this is only the case for the intervention group), so patients may calculate their risk score. The medical/dental assistant will be available for questions during this process. The further course differs depending on the study and risk-score.

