#### Dentist study

For the primary outcome, we will test the null hypothesis H_0_^ZA^: π_IG_^T1−T0^ = π_KG_^T1−T0^ against the alternative hypothesis H_1_^ZA^: π_IG_^T1−T0^ ≠ π_KG_^T1−T0^ on a two-sided significance-level of 5%. π_IG_^T1−T0^ and π_KG_^T1−T0^ represent the rate of new diabetes diagnoses between baseline (T0) and after 12 months (T1) in both groups.

Primary analysis will be performed using a generalized, logistic mixed model adequately representing the multi-level structure of data (practice on level 1, patients on level 2). For the test of H_0_^ZA,^ the „rate of new diabetes diagnoses between T0 and T1” will be used as the dependent variable. The model contains the practice as a random effect and the group (intervention vs. control), age, sex, insurance status, state and residential area as fixed effects on the patient level.

It can be assumed that claims data will be complete and missing values will only occur in the additional study data and the questionnaires. Missing values of the primary outcome will be imputed using multiple imputation [27] while accounting for the baseline-variables age, sex, insurance status and residential area. To check for the sensitivity of results, assumptions on missing values will be analyzed and an alternative procedure to handle missing data, such as an analysis of the full dataset, will be looked into. Further sensitivity analyses include sub-group analyses for both states and for insurance status.

Secondary endpoints will be presented descriptively first. Where appropriate, secondary endpoints will be explored similar to the primary analysis. For binary endpoints, logistic regression analyses will be performed. For continuous endpoints, linear regression analyses will be performed. For all estimated effects we will present descriptive p-values and 95% confidence intervals. All analyses are performed using a validated R environment with R version 4.0.0 or higher. The primary analysis is independently counter-programmed in SAS version 9.4 or higher.

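### As written, dental practices can recognise their arm before they count as included, and unblinded assistants then enrol the patients; concealing the sequence does not prevent selection at either step

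*Protocol article*

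**What the plan says.** The Recruitment section of the protocol article gives one sequence for both studies. An interested practice is sent the study information, the consent forms and "The required authorization form to include the practice in the care contract with the insurer (intervention groups only". The next step is: "As soon as the authorization form and each form of consent is returned dated and signed by the respective person, the practice is included". The practice ID and database log-in follow, and patient recruitment starts once the practice has entered its basic data.

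The practice's own staff find the patients: "Medical/dental assistants identify eligible patients according to the inclusion criteria (Table 1) when they visit the practice". The same assistant informs them, countersigns the consent and transfers the data. Under Primary endpoints, dental assistants also record the new diagnoses at T1.

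Under Randomization procedure, Dentist study, practices are assigned 1:1 by a central web tool "to avoid any manipulation and ensure concealed allocation". Randomisation is stratified by state, and blocks of varying length are said to keep the groups equal and to avert selection bias.

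Under Baseline survey (T0), patients in both arms give sociodemographic data and self-reported conditions. For the risk questions the text says that "in the dentist study, this is only the case for the intervention group". The primary model of the dentist study adjusts for age, sex, insurance status, state and residential area.

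**The concern.** Randomising practices protects the comparison only if two things hold. The practices that enter each arm must be the ones assigned to it, and the patients enrolled must not depend on the arm. The described sequence leaves both open. A form that only one arm receives, sent before inclusion, tells a dental practice which arm it is in, and a practice that then declines never appears as included. Patients are enrolled later still, by staff who know the arm.

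The tested parameters "represent the rate of new diabetes diagnoses between baseline (T0) and after 12 months (T1) in both groups". That proportion depends heavily on the diabetes risk of whoever is enrolled. If intervention practices tend to enrol patients who look at risk, diagnoses rise there without any intervention effect. Selection the other way would hide a real effect. The dentist study is the only randomised comparison in the project, so this is where the protection matters most.

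**Working it through.** **Step 1: does the form separate the dental arms?** The restriction to intervention groups is written for both studies. In the GP study every recruited practice is an intervention practice, because its control group is calculated from claims and DMP data. The Written survey paragraph of the process evaluation agrees: 331 intervention practices = 248 GP + 83 dental. The only recruited practices that the restriction can exclude are the 83 dental control practices. A form sent on that basis before inclusion therefore requires the dental arm to be fixed already, and it shows the arm to the practice.

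**Step 2: can the enrolling assistant be blind?** No. Only intervention practices join the care contract (Recruitment) and use the T2DM risk questions (Baseline survey). Patient recruitment starts after practice inclusion, hence after allocation on this reading.

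**Step 3: what does the randomisation method protect?** A central tool with variable blocks stops anyone foreseeing the next practice's assignment. It has no bearing on whether a practice proceeds once it knows its arm, or on which eligible patients are approached.

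**Step 4: reproduce the planned size.** Inputs from Sample size calculation, Dentist study: rates 0.05 and 0.10, α = 0.05, power 0.80, ICC 0.03, 8 patients per practice. The calculation "is therefore based on a Z-Test with non-pooled variance", and the two-sided level comes from the hypotheses section.

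- n = (0.05×0.95 + 0.10×0.90) × (1.960 + 0.842)² / 0.05² = 431.7, so 432 per arm
- Design effect = 1 + (8 − 1)×0.03 = 1.21; 432 × 1.21 = 522.7; 522.7/8 = 65.3, so 66 practices = 528 patients
- 66/0.8 = 82.5, so 83 practices = 664 patients

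Both stated figures reproduce. The point does not change the sample size.

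**Step 5: illustrate selection with no true effect.** The shifts are assumptions; the documents give none. SE = √[(p_C q_C + p_I q_I) × 1.21/528], with p_C = 0.05. The rejection probability is Φ(d/SE − 1.96) + Φ(−d/SE − 1.96), with d = p_I − 0.05.

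| Intervention-arm rate from selection alone | SE | d/SE | Two-sided rejection |
|---|---|---|---|
| 5% | – | 0 | 5.0% |
| 6% | 0.0154 | 0.65 | 9.9% |
| 7% | 0.0161 | 1.25 | 23.8% |

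In terms of case mix, suppose 12-month diagnosis rates of 10% in high-risk and 2.5% in low-risk patients (also an assumption). One third high-risk gives the 5% control rate: 1/3×10% + 2/3×2.5%. Enrolling 60% high-risk patients gives 0.6×10% + 0.4×2.5% = 7%.

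**Step 6: the other direction.** At the planned 10% the same formula gives a power of 80.4%. If selection lowers the intervention-arm rate to 9% or 8%, power falls to 64.2% or 43.7%.

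**The case against.** The strongest objection is that the article never says when the web tool is run or when the result is disclosed. The Recruitment text merges GP practices with both dental arms. Its inclusion rule cannot be literal for control practices, which have no authorization form to return. A condensed article may leave the mailing order, a sampling rule and a screening log to the full protocol. This stands as a limit: knowledge of the arm before inclusion is an inference from the stated order, not a stated fact.

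A reader might go further in four ways that the documents do not support.

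- **That the Recruitment section contradicts the concealed allocation.** Concealment there concerns the sequence, and it can hold even if practices later decline. What overreaches is the claim to avert selection bias.
- **That the 25 Euros per recruited patient drives selection.** It is paid in all practices whatever the patient's risk, so it gives no reason for arms to differ.
- **That assistants select on the risk score.** The score is completed after consent, so only an impression of risk could guide them. The eligibility criteria are the same in both arms.
- **That risk imbalance can be neither seen nor adjusted.** Only the score is missing in controls. Age and sex are in the model, and self-reported conditions are collected in both arms, which gives a partial view.

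The error rates come from an unadjusted test, whereas the planned model would remove part of any imbalance.

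**Conclusion.** The point holds in limited form. That patients are enrolled after practice inclusion by unblinded staff follows directly from the text. That dental practices can recognise their arm before they count as included follows from the order described, on the assumption that the order is followed as written. The randomisation method guards against neither, so its stated protection against selection bias is too broad.

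The documents give neither the size nor the direction of any bias. The figures of about 10% and 24% show sensitivity only: a shift of one percentage point, against a planned effect of five, roughly doubles the type I error in an unadjusted test. They are not estimates of what will happen, and it would be too strong to say that randomisation has lost its value. The remedy is cheap and touches neither the endpoint nor the sample size, so the change should be made.

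**What to change.** 1. Send every interested dental practice the same pack. Run the randomisation only after the practice consents are returned, and send the authorization form afterwards. Count the practice as randomised from that moment and report by arm any that leave. For practices already enrolled, report refusals after allocation by arm.
2. Have each practice invite consecutive eligible patients up to its target, with an anonymous log of those eligible but not enrolled.
3. Compare baseline characteristics by arm. As a sensitivity analysis, add diabetes-relevant self-reported conditions to the primary model, provided the T0 questionnaire collects them in both arms; the article does not list the items.
4. Limit the claim in the randomisation section to concealment of the sequence.

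The cost is a reordered mailing, a short log per practice and a few lines of analysis text. The downside is some dilution under intention-to-treat if intervention practices do not return the form. For example, if one in ten still enrolled patients but gave usual care (an assumption), the expected difference would shrink from 5 to 0.9 × 5 = 4.5 percentage points.
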